## **1 Introduction**

This is the Statistical Analysis Plan (SAP) for the study CIBI362A101 "A Multiple Dose Tolerability and Pharmacodynamic Study of IBI362 in Chinese Patients with Type 2 Diabetes and Inadequate Glycemic Control" (Protocol No.: CIBI362A101, Version 1.1, Date 2021-01-15). This SAP summarizes the design and objectives of the study and is intended to provide a detailed definition of the endpoint measures in the protocol and a detailed description of the planned statistical analyses. The final SAP will be approved and signed prior to database lock.

## **2 Protocol Details**

### **2.1 STUDY OBJECTIVES**

- Primary objective
  - To investigate the safety and tolerability of multiple subcutaneous injections of IBI362 in patients with type 2 diabetes inadequately controlled by lifestyle intervention or metformin, and to determine the safe dose range for its clinical use.
- Secondary objectives
  - To investigate the pharmacokinetic/pharmacodynamic (PK/PD) parameters of multiple subcutaneous injection of IBI362 in patients with type 2 diabetes inadequately controlled by lifestyle intervention or metformin.

### **2.2 STUDY DESIGN**

The study was planned to include 42 patients with type 2 diabetes who failed to achieve HbA1c control after at least 2 months of lifestyle intervention or stable dose of metformin ( $\geq 1000$  mg/day or maximum tolerated dose). The study was divided into three cohorts, which were Cohort 1 (n = 14), Cohort 2 (n = 14), and Cohort 3 (n = 14), and patients in each cohort were randomly divided into IBI362 treatment group (n = 8), placebo group (n = 4), and dulaglutide 1.5 mg treatment group (n = 2) in an 8:4: 2 ratio. The active comparator drug, dulaglutide, was administered at 1.5 mg QW for 12 weeks in Cohorts 1, 2, and 3, and the dosing schedules for IBI362 and placebo are described below:

Cohort 1: The initial dose is 1.0 mg once weekly for 4 weeks. If well tolerated, the dose should be increased to 2.0 mg once weekly. After 4 weeks of treatment, the subject's tolerance should be evaluated again. If well tolerated, the dose should be increased to 3.0 mg once weekly for 4 weeks (escalation by 1 mg every 4 weeks to the target dose).

Cohort 2: The initial dose of the subject is 1.5 mg, once weekly for 4 weeks. If well tolerated, the dose will be increased to 3.0 mg, once weekly for 4 weeks. After that, the subject's tolerance will be evaluated again. If 3.0 mg cannot be tolerated according to the intolerance criteria, the subject need to initiate the next dose according to Cohort 2 (backup 1); if 3.0 mg is well tolerated, the dose will be increased to 4.5 mg, once weekly for 4 weeks. If 4.5 mg can not be tolerated according to the intolerance criteria, the subject need to initiate the next dose according to Cohort 2 (backup 2) (escalation by 1.5 mg every 4 weeks to the target dose).

Cohort 2 (backup 1): If 3.0 mg cannot be tolerated, the dose should be reduced to 2.25 mg after 1-week break and continued to be increased to 3.0 mg after 2-week treatment. If well tolerated, the dose should be increased to 3.0 mg and administered for 4 weeks.

Cohort 2 (backup 2): If 4.5 mg cannot be tolerated, the dose should be reduced to 3.75 mg after 1-week break and administered for 2 weeks till the end of the trial.

Cohort 3: Subjects should not start dosing until subjects in Cohort 2 complete the initial 4-week evaluation at 1.5 mg dose. If subjects in Cohort 2 cannot tolerate 1.5 mg, 2.0 mg and higher doses will not be explored in Cohort 3. The initial dose of subjects in this cohort was 2.0 mg once weekly for 4 weeks. If well tolerated, the dose will be increased to 4.0 mg once weekly. After 4 weeks of administration, the subject's tolerance will be evaluated again. If well tolerated, the dose will be increased to 6.0 mg once weekly for 4 weeks (escalation by 2 mg every 4 weeks to the target dose).

The trial consisted of a 3-week screening period, a 12-week double-blind treatment period, and an 8-week safety follow-up period.

## **2.3 SAMPLE SIZE AND POWER**

42 patients were enrolled in 3 dose cohorts. A total of 14 subjects were enrolled in each cohort at a ratio and randomized 8:4:2 to IBI362, placebo, and active control drug.

## **2.4 RANDOMIZATION AND MASKING**

This is a randomized, double-blind trial of IBI362 versus placebo within each dose group. At each dose, subjects were randomized to receive IBI362, placebo, active control treatment in a ratio of 8:4:2. If a subject is assigned to receive IBI362 or placebo, the subject, the investigator, and all medical personnel involved in the treatment or clinical evaluation will be blinded to the treatment allocation from the time of randomization until the database is locked, as follows:

Different drug numbers were linked to random numbers in the central randomization system, and the blind base of drug numbers and random numbers remained masked to subjects and investigators throughout the trial. The randomization table was kept by a designated person.

The study drug and placebo will be packaged, labeled, administered at the same time, and will have the appearance, taste, and smell exactly the same to mask the real situation of the treatment drug.

Unblinding can only be performed in case of emergency and at the end of the study.

If a subject is randomized to receive active control, the subject will not be blinded.

## **2.5 CHANGES TO PLANNED STATISTICAL ANALYSES IN THE PROTOCOL**

### **2.5.1 Changes to Statistical Analysis in Protocol Amendments**

There were no statistical analysis changes in this protocol amendment.

### **2.5.2 Changes to Planned Analyses in the Statistical Analysis Plan**

| Protocol                                                                                                                                                                                                                   | Statistical Analysis Plan                                                                                                                                                                                                                                                                                                  |                                                                                                                     |
|-----------------------------------------------------------------------------------------------------------------------------------------------------------------------------------------------------------------------------------|-----------------------------------------------------------------------------------------------------------------------------------------------------------------------------------------------------------------------------------------------------------------------------------------------------------------------------------|---------------------------------------------------------------------------------------------------------------------|
| Statistical description in the protocol                                                                                                                                                                                    | Statistical description in statistical analysis plan                                                                                                                                                                                                                                                                       | Reason for change                                                                                            |
| Efficacy Analysis Set: Subjects in the Safety Set who had at least 1 postbaseline assessment.                                                                                                                                     | 
Efficacy Analysis Set: Subjects in the Safety Set who had at least 1 postbaseline assessment (glycated hemoglobin).
 
Anti-drug Antibody Analysis Set: includes subjects who have taken at least one dose of study treatment and have at least one post-dose valid ADA test result. Used for immunogenicity analysis.
 | Add the specific description of anti-drug antibody analysis set and refine the definition of efficacy analysis set. |
| To assess the pharmacodynamic parameters of IBI362 after multiple doses: changes in fasting blood glucose, glucagon, insulin, fasting C-peptide, HbA1c, endogenous oxyntomodulin (OXM) and GLP-1 before and after administration; | To assess the pharmacodynamic parameters of IBI362 after multiple doses: changes in fasting blood glucose, insulin, fasting C-peptide, HbA1c, endogenous oxyntomodulin (OXM) and GLP-1 before and after administration;                                                                                                           | Analysis of glucagon was not done due to lack of data.                                                              |
| Changes in fasting blood glucose, insulin and glucagon at steady state in each dose phase during dose escalation;                                                                                                                 | Changes in fasting blood glucose and insulin at steady state in each dose phase during dose escalation;                                                                                                                                                                                                                           | Analysis of glucagon was not                                                                                        |

| Protocol                                                                                                                                                                                                                                                                                                                                                                                                                                                                                                                                                                                                                                                                                                                                                                                                                                                                                                                                                                                                                                                            | Statistical Analysis Plan                                                                                                                                                                                                                                                                                                                                                                                                                                                                                                                                                                                                                                                                                                                                 |                                                                                                                                                                                                                                                            |
|---------------------------------------------------------------------------------------------------------------------------------------------------------------------------------------------------------------------------------------------------------------------------------------------------------------------------------------------------------------------------------------------------------------------------------------------------------------------------------------------------------------------------------------------------------------------------------------------------------------------------------------------------------------------------------------------------------------------------------------------------------------------------------------------------------------------------------------------------------------------------------------------------------------------------------------------------------------------------------------------------------------------------------------------------------------------|-----------------------------------------------------------------------------------------------------------------------------------------------------------------------------------------------------------------------------------------------------------------------------------------------------------------------------------------------------------------------------------------------------------------------------------------------------------------------------------------------------------------------------------------------------------------------------------------------------------------------------------------------------------------------------------------------------------------------------------------------------------|------------------------------------------------------------------------------------------------------------------------------------------------------------------------------------------------------------------------------------------------------------|
| Statistical description in the protocol                                                                                                                                                                                                                                                                                                                                                                                                                                                                                                                                                                                                                                                                                                                                                                                                                                                                                                                                                                                                                             | Statistical description in statistical analysis plan                                                                                                                                                                                                                                                                                                                                                                                                                                                                                                                                                                                                                                                                                                      | Reason for change                                                                                                                                                                                                                                          |
|                                                                                                                                                                                                                                                                                                                                                                                                                                                                                                                                                                                                                                                                                                                                                                                                                                                                                                                                                                                                                                                                     |                                                                                                                                                                                                                                                                                                                                                                                                                                                                                                                                                                                                                                                                                                                                                           | done due to lack of data.                                                                                                                                                                                                                                  |
| 
All efficacy analyses were performed on the efficacy analysis set. Efficacy endpoints will be analyzed only descriptively. For continuous efficacy endpoint indicators, the corresponding means and 95% confidence intervals will be calculated for IBI362 subjects in each dose group, all placebo subjects and all active control subjects, respectively. A two-sample t-test will be used to calculate the p-value of IBI362 versus placebo for each dose group and provide the corresponding point estimate and 95% confidence interval of the difference. LOCF missing values will be used for imputation. For the categorical efficacy endpoints, the ratio within each dose group will be calculated and the 95% confidence interval within the group will be calculated using Clopper-Pearson; the difference between IBI362 placebo groups will be compared using the chi-square test and the corresponding 95% confidence interval will be calculated. Missing values for grouped endpoints will be imputed using the default non-response method.
 | 
Analysis of HbA1c was performed in the efficacy analysis set, analysis of pharmacodynamic parameters was performed in the PD analysis set, and other efficacy endpoint indicators were performed in the safety analysis set unless otherwise specified. For continuous efficacy endpoint indicators, mixed model repeated measures (MMRM)/ANCOVA model was used to estimate the point estimate and 90% confidence interval of each treatment group, and the point estimate and 90% confidence interval of the difference between each IBI362 treatment group/dulaglutide group and placebo. LOCF missing values will be used for imputation. Nominal p-values are provided for comparisons. No multiplicity adjustment will be made in this trial.
 | 
The primary endpoints of this trial are safety and tolerability. The number of subjects in each treatment group is small. 90% confidence interval will be provided. No multiplicity adjustment will be made. Only nominal p value will be provided.
 |

### **3 Endpoints**

#### **3.1 SAFETY, TOLERABILITY AND MAXIMUM TOLERATED DOSE EVALUATION**

- Safety and tolerability: During dose escalation, the incidence and severity of adverse events at each dose level, including chief complaint, physical examination, laboratory tests (hematology, blood chemistry, lipid panel, coagulation function, urinalysis, myocardial enzymes, serum amylase and/or lipase, thyroid function, calcitonin, etc.), vital signs (pulse, respiration, blood pressure, body temperature), 12-lead ECG and other examinations; treatment compliance; and record the name, clinical characteristics, severity, start and stop time, supportive care and outcomes of adverse events, correlation with the study drugs;
- Maximum tolerated dose: If the dose exploration is stopped when the criteria for stopping dose escalation are met at a certain dose level, the previous dose is the maximum tolerated dose. If the criteria are still not met when the maximum exploratory dose is reached, the maximum tolerated dose is greater than or equal to the maximum escalation dose.

#### **3.2 IMMUNOGENICITY**

- The incidence of anti-IBI362 antibody (ADA) and neutralizing antibody (NAb) in before and after dosing;

#### **3.3 PHARMACOKINETIC PARAMETERS**

- To evaluate the kinetic parameters of IBI362 in patients with type 2 diabetes, including but not limited to: time to peak plasma concentration ( $T_{max}$ ), peak plasma concentration ( $C_{max}$ ), area under the concentration-time curve (AUC), volume distribution (Vd), half-life ( $T_{1/2}$ ), clearance (CL), accumulation ratio (AR), etc.;

#### **3.4 PHARMACODYNAMIC PARAMETERS**

- To assess the pharmacodynamic parameters of IBI362 after multiple doses: changes in fasting blood glucose, insulin, fasting C-peptide, HbA1c, endogenous OXM and GLP-1 before and after administration;
- Changes in fasting blood glucose and insulin at steady state in each dose phase during dose escalation;
- The change of each parameter of MTT test from baseline after multiple dose administration;

### **3.5 OTHER EFFICACY MEASURES**

- Self-measured blood glucose;

### **3.6 EXPLORATORY MEASURES**

- To evaluate the effect of IBI362 on weight loss (changes in body weight, waist circumference and BMI);
- To assess the improvement of islet in IBI362: changes in islet  $\beta$  function (HOMA-Beta) and insulin resistance (HOMA-IR).

## **4 Analysis Datasets**

### **4.1 ANALYSIS DATASETS**

Safety Set: subjects who signed informed consent and received at least one dose of the study drug.

Efficacy Analysis Set: Subjects in the Safety Set who had at least 1 postbaseline assessment (glycated hemoglobin).

PK analysis set: including all the subjects who receive at least one dose of the investigational drug and have at least one effective concentration data of the detected components after medication.

PD analysis set: including all subjects who receive at least one dose of the study drug and have valid test results at baseline and after at least one dose.

Anti-drug Antibody Analysis Set: includes subjects who have taken at least one dose of study treatment and have at least one post-dose valid ADA test result. Used for immunogenicity analysis.

## **5 Data processing**

### **5.1 GENERAL SPECIFICATIONS**

### **5.2 EFFICACY DATA HANDLING PRACTICES**

In this trial, efficacy data will be analyzed as it is and, if not otherwise specified, missing values will not be imputed.

### **5.3 MISSING VALUES AND OUTLIERS**

- **Handling of Related Variables Calculated if Baseline Data Date is Missing**

Without affecting the logic, impute as follows:

- If day/month/year are all missing, no imputation will be done;
- If the day and month are missing, impute it to July 1 unless contradicts with other dates;
- If the date is missing, impute day to 15 unless contradicts with other dates.

- **Handling of completely/partially missing values for prior/concomitant/non-drug therapy dates**

If the start/end dates or time of prior/concomitant medication/non-drug therapy are completely or partially missing, no imputation is needed. Completely or partially missing situations where it is impossible to determine prior or concomitant will be treated as concomitant.

In the analysis of duration of specified concomitant medication, if the end time is missing, impute it to the data cutoff date, death date or withdrawal date, whichever is earlier.

- **Handling of Completely/Partially Missing Adverse Event Dates**

If the AE start date is completely or partially missing, and it is not clear whether the data already collected in the eCRF is before or after the first dose of study treatment, the AE is considered to be a treatment-emergent AE. If it is necessary to calculate the duration of adverse event or mark the cycle number of adverse events, the completely/partially missing start/end dates will be imputed as follows without affecting the logic:

- If day/month/year of the start date are all missing, impute it to the date of first study treatment;
  - If month and day of the start date are missing and it is in the same year as the first study treatment date, unless contradict with other collected data (such as end date, etc.), impute it to the first study treatment date, otherwise July 1st,
  - If only the day is missing and there is no contradiction with other collected data (such as end date, etc.), and it is in the same year and month as the first study treatment date, impute it to the first study treatment date, otherwise impute it to day 15,
  - If the imputed start date is after the end date, it should be set to the end date,
  - If day/month/year of the end date are all missing, it shall be considered as a continued adverse event;
  - If the month and day of the end date are missing (or only day is missing), then impute it to the last day of the known year (or month and year).
- **Treatment-emergent adverse event designation when start date/time of first study treatment is missing**

Adverse events that occurred on or after randomization will be considered treatment-emergent.

The imputation rule of completely/partially missing dates will only be used to flag or derive variables for the analysis, and the original dates as recorded on the eCRF will be presented in the listings.

- **Missing Adverse event relationship to study drug**

An adverse event will be considered related if its relationship to study drug is missing.

- **Missing Adverse Event Severity**

In the analysis by severity grade, adverse events with missing severity grade will be counted in the number/frequency of severe cases.

Subjects with missing baseline values will be classified as "missing" in the cross-tabulation of baseline vs. worst post baseline results.

- **Handling of outliers**

Outlier will be analyzed as it is.

- **Other Data Handling Considerations**

If the reported value of a laboratory parameter cannot be used in the statistical summary tables (e.g., the value of a numeric parameter is reported as a string), the coded value will be determined appropriately and used in the statistical analysis. Values higher than the upper limit of the test will be added 0.0001, e.g. "> 100" will be treated as "100.0001"; values lower than the lower limit of the test will be subtracted by 0.0001, e.g. "< 100" will be treated as "99.9999". The actual values reported in the database will still be presented in the listings.

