14. Blood samples for HbA1c will be collected at screening, within 1 h prior to dosing on D1 of Week 1, within 1 h prior to dosing on D29 of Week 5, within 1 h prior to dosing on D57 of Week 9, and at 168 h  $\pm$  12 h (D85) after dosing on D78 of Week 12. If a patient fails to complete the study and withdraws from the study prematurely, samples will be collected at the early termination visit. Two (2) mL will be collected at each collection point and the detailed procedures will be described in the central laboratory manual.
15. Immunogenicity sample will be collected in Week 1 (within 1 hour before the start of infusion), Week 5 (within 1 hour before infusion on D29), Week 9 (within 1 hour before infusion on D57), Week 13 (168 hours  $\pm$  12 hours after Week 12 administration) and safety follow-up visit. If a patient withdraws prematurely. An immunogenicity sample should also be collected at early termination visit as far as possible. Collect 5 mL at each blood collection point. Refer to the central laboratory manual for the detailed operation process.
16. The PK/PD sampling points are detailed in Table 3.
  - Central laboratory test.

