### **6.6.1 Adverse events**

Classified by date of event:

- Pre-treatment Adverse Events: Adverse events that occurred from signing of informed consent until the first dose of study treatment.
- Treatment-emergent adverse events (TEAEs): Adverse events that occurred or became serious during the first dose of study treatment through 56 days after last dose.
- Post-treatment adverse events: Adverse events that occurred or became serious after 56 days following the last dose until the end of the trial.

If the AE start date is completely/partially missing, impute the date according to Section 5.3 before assigning pre-treatment/on-treatment/post-treatment adverse events.

The incidence (frequency) of all AEs, TEAEs, severe TEAEs, TEAEs leading to permanent treatment discontinuation, drug-related TEAEs (TRAEs), severe TRAEs, TRAEs leading to permanent treatment discontinuation, AESIs, severe AESIs, AESIs leading to permanent treatment discontinuation, SAEs, SAEs related to study drug, and SAEs leading to permanent treatment discontinuation will be summarized by treatment group.

The following categories of adverse events will be summarized by SOC, PT, and SOC, PT, and severity from MedDRA coding:

- TEAEs
- TEAE leading to permanent discontinuation
- TRAE
- TRAEs leading to permanent discontinuation
- AESI
- AESIs leading to permanent discontinuation
- For gastrointestinal reactions, the number of events with gastrointestinal reactions was also provided. Gastrointestinal reactions including adverse reactions with preferred terms of nausea, vomiting, diarrhea, dyspepsia, abdominal distension, abdominal discomfort, and gastroesophageal distress

TEAEs will also be summarized by PT in MedDRA and the number of events of TEAEs will be calculated.

Treatment-emergent SAEs, treatment-emergent SAEs related to study drug, and treatment-emergent SAEs leading to permanent discontinuation will be summarized by SOC and PT.

Hypoglycemic events will be summarized by treatment group.

The above summary tables are sorted according to the incidence of AEs in all subjects who received IBI362.

Subjects who discontinued treatment due to AEs, subjects who experienced SAEs, and subjects who died will be listed (at least include AE start date, end date, severity, relationship with drug, action taken, and outcome). All AEs will be listed.

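### The AE start-date imputation (1 July or day 15) has no upper bound, so a treatment-emergent event whose end date does not fall inside the window can be classed as post-treatment

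*Combined protocol and SAP*

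**What the plan says.** SAP 6.6.1 defines treatment-emergent events as "Adverse events that occurred or became serious during the first dose of study treatment through 56 days after last dose". Later events, up to the end of the trial, are post-treatment. For partial start dates the instruction is to "impute the date according to Section 5.3 before assigning pre-treatment/on-treatment/post-treatment adverse events".

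SAP 5.3 supplies the dates:

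- Month and day missing: the first-dose date if the year matches, and if not 1 July ("impute it to the first study treatment date, otherwise July 1 st").
- Day missing: "impute it to the first study treatment date, otherwise impute it to day 15".
- A correction to the imputed start: "If the imputed start date is after the end date, it should be set to the end date".
- Missing end dates: "If day/month/year of the end date are all missing, it shall be considered as a continued adverse event". An end date with only the year known goes to the last day of that year; with only the day missing, to the last day of that month.

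SAP 5.3 also counts an event as treatment-emergent by default when "it is not clear whether the data already collected in the eCRF is before or after the first dose of study treatment". It introduces the imputation as something needed for event duration or cycle number, under a general proviso that it must not upset the logic of the data.

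**The concern.** Every limit in SAP 5.3 concerns the first dose or the event's own end date. None refers to last dose + 56 days or to the patient's last contact. The treatment-emergent default does not close the gap: an event dated only 2021 in a patient first dosed in December 2020 is plainly after first dose, so there is no doubt of the kind that triggers the default.

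Safety is the primary objective, and each IBI362 arm has 8 patients, so losing one patient from a row of the treatment-emergent table moves that incidence by 1/8 = 12.5 percentage points. The rule also runs against the rest of SAP 5.3, which counts a missing drug relationship as related and a missing severity as severe.

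**Working it through.** **Inputs.** Last dose on D78 (notes to protocol Table 2, HbA1c sampling: "after dosing on D78 of Week 12"), with a visit window of ±2 days. Tail of 56 days (SAP 6.6.1). Safety follow-up visit on D134 (protocol Table 2).

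**Window end.** 78 + 56 = D134, which reproduces the follow-up day in the schedule. The window is the first-dose date plus 133 days.

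**1 July rule.** It can reach an in-window event only if the window crosses a year end. For 2020 that means first doses from 21 August to 31 December: 133 of 366 dates. The latest window end belongs to a first dose on 31 December 2020: 31 December + 133 days = 13 May 2021. From 13 May to 1 July is 49 days. Over all first-dose dates in 2019–2024, 798 windows cross a year end and 1 July falls inside none of them.

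| Last dose | Tail | Smallest gap to 1 July |
|---|---|---|
| D78 | 56 days | 49 days |
| D80 | 56 days | 47 days |
| D78 | 90 days (AE period in protocol 8.1) | 15 days |
| D80 | 90 days | 13 days |

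Earlier discontinuation shortens the window and widens the gap.

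*Example.* First dose 1 December 2020, last dose 16 February 2021, window end 13 April 2021. An ongoing event dated 2021 becomes 1 July 2021, 79 days past the window. If the same event had a known end date of 20 January 2021, the start would be reset to that day and the event would stay treatment-emergent.

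**Effect of the end-date reset.** Assume first doses uniform over 2020 and true starts uniform over the window. In-window starts in the following year number 1 + 2 + … + 133 = 8,911. With a known end date and a duration of *d* days, the reset start stays in the window for (133 − d)(134 − d)/2 of them.

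| Duration (days) | Kept | Share of 8,911 |
|---|---|---|
| 0 | 8,911 | 100% |
| 7 | 8,001 | 90% |
| 14 | 7,140 | 80% |
| 30 | 5,356 | 60% |
| 60 | 2,701 | 30% |

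If the event is ongoing, or its end date is missing, year-only or past the window, none is kept.

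**Day-15 rule, before the reset.** It pushes an event out only if the window closes on day 1 to 14 of a month and the event starts in that month on or before the closing day. Over the 48 months of 2020–2023:

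- First-dose dates exposed: 48 × 14 = 672 of 1,461 = 46%.
- In-window days affected: 48 × (1 + … + 14) = 48 × 105 = 5,040 of 1,461 × 134 = 195,774, or 2.6%.
- Earliest affected start: 13 days before the window closes, that is 56 − 13 = 43 days after last dose.

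*Example.* First dose 28 September 2020, last dose 14 December 2020, window end 8 February 2021. An ongoing event starting on 3 February 2021 with the day missing becomes 15 February, and post-treatment.

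**The case against.** The strongest reply is that SAP 5.3 already protects most records. The end-date reset keeps any event with a known end date inside the window, and the proviso about logic arguably bars a 1 July onset that falls after the patient's last visit, since protocol 8.6.1 collects events only to the end of the study. The first part stands. The second stands only halfway: the proviso may forbid the date, but it names no replacement, so the programmer has no rule to follow.

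It can also be said that partial dates will be rare. Doses are given at the site, events are recorded at every visit, start and stop times are required, and missing data are queried. That is fair and limits the weight of the point.

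SAP 5.3 can also be read as imputing only for duration or cycle number, so that it never decides the period. SAP 6.6.1 says otherwise in terms, and 5.3 itself later allows imputed dates for flagging or deriving analysis variables. The two sections need reconciling.

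Four stronger readings are tempting and are not supported:

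- *The 1 July rule misclassifies every event it touches.* True of the imputed date before the reset, not of the final classification. The matching figure, 8,911 of 366 × 134 = 49,044 in-window days (18.2%), holds only if no end date brings the start back.
- *Day 15 removes events that occur during dosing.* The affected starts are all at least 43 days after last dose.
- *All AESI and SAE tables lose events.* SAP 6.6.1 does not restrict its AESI entries, or SAEs in the overview, to treatment-emergent events. All AEs are summarised and listed, and listings keep the dates as recorded.
- *Treatment-emergent events are the primary endpoint.* Protocol 2.2.1 speaks of adverse events at each dose level.

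**Conclusion.** The gap is real and minor. As written, a year-only start in the year after first dose is always dated past the window, by at least 49 days (47 if the last dose is on D80). The event is then classed as post-treatment whenever its end date is missing, ongoing, year-only or later than the window. The day-15 rule can produce the same error for at most 2.6% of in-window days, and for about 46% of first-dose dates. The tables affected are those of treatment-emergent and drug-related treatment-emergent events.

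The percentages assume uniform first-dose dates and event timing. The documents give no enrolment dates: protocol versions of March 2020 and January 2021 and a SAP of June 2021 make windows crossing from 2020 into 2021 plausible, but do not prove them. The number of partial dates is unknown and probably small.

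**What to change.** Add to SAP 5.3: an adverse event whose known date parts do not exclude a start between first dose and last dose + 56 days is classed as treatment-emergent, and its imputed start is capped at the earliest of its end date, the last contact and last dose + 56 days. Otherwise keep the existing imputation. Moving every partial date to the earliest possible day would also close the gap, but it could shift events to a lower dose level, and the primary endpoint is reported by dose level.

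In the same edit, make 5.3 and 6.6.1 agree on whether imputed dates are used for period assignment or only for duration and cycle marking.

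The cost is a sentence or two in the SAP and a minimum function in the derivation program. No complete date changes, and no event provably outside the window is moved into it.
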